**Method:**

This is a randomized, double-blind, placebo-controlled trial. A total of 120 eligible patients with GERD will be randomized into the experimental group or the control group. The treatment includes two phases: the initial treatment period lasts 8 weeks (weeks 1–8), and the maintenance treatment period lasts 4 weeks (weeks 9–12). During the initial treatment period, the experimental group will take rabeprazole and LiHuo probiotics, and the control group will take rabeprazole and a probiotic placebo; during the maintenance treatment period, the experimental group will take LiHuo probiotics, and the control group will take a probiotic placebo. The primary measure is the change in the GM. The secondary measures are the Reflux Disease Questionnaire (RDQ) score, Gastrointestinal Symptom Rating Scale (GSRS) score, faecal metabolome (FM), body mass index, Los Angeles grade of oesophagitis, adverse event (AE) rate and treatment compliance. Each outcome indicator will be assessed at day 0 (before administration), day 28 and/or 56 (during administration), and day 84 (end of administration) to reveal intragroup differences. AEs will be monitored to assess the safety of LiHuo probiotics.

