### Exclusion criteria

Use of GERD-related drugs such as acid inhibitors, antacids, prokinetics, gastric mucosal protectors, and herbs (see Additional file 1: Appendix 4) or probiotics and probiotic-related preparations in the last 2 weeks; Any of the following conditions:Liver insufficiency, defined as alanine aminotransferase (ALT) or aspartate aminotransferase (AST) > 2 × the upper limit of normal (ULN);Renal insufficiency, defined as serum creatinine (Scr) > 1 × ULN;Heart failure or electrocardiogram (ECG) abnormalities;Peptic ulcer and bleeding, oesophageal gastric varices, or upper gastrointestinal malignancies confirmed by endoscopy at tertiary hospitals in China in the last 3 months; Myocardial infarction, stroke, or malignant tumour; History of gastro-oesophageal or duodenal surgery; Plans to become pregnant or father a child in the near future, or pregnancy or breastfeeding in women. Inability to cooperate, such as an inability to understand the informed consent form or unwillingness to provide personal information; Allergies to the study drug (rabeprazole) or probiotics; Oesophagitis caused by gastric retention and pyloric obstruction.

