### Intervention strength and management

Rabeprazole: 10 mg/tablet, from Eisai China, Inc (Tokyo, Japan).

LiHuo Probiotics powder: LiHuo probiotics powder containing strains such as *Lactobacillus casei Zhang*, *Bifidobacterium lactis* V9, and *Lactobacillus plantarum* P9, 2 g/bar, each bar containing active probiotics (≥ 50 billion CFU), were obtained from Jiangzhong Pharmaceutical Company Limited (China). During the manufacturing of LiHuo probiotics powder, *Lactobacillus casei Zhang*, *Bifidobacterium lactis* V9, and *Lactobacillus plantarum* P9 were mixed according to concentrations of ≥ 5 billion CFU/g, ≥ 15 billion CFU/g, and ≥ 5 billion CFU/g, respectively.

Probiotic placebo powder: The ingredients are maltodextrin, orange powder, and maltitol, and there are no active ingredients. The appearance, packaging, storage method, and dosing are the same as those of the LiHuo probiotics from Jiangzhong Pharmaceutical Company Limited (China).

The rabeprazole, LiHuo probiotics, and probiotic placebo will be stored in a cool, dry place away from light. Refrigerated storage will retain the maximum activity of the product. Each patient will receive a sample that corresponds to his or her unique number. All remaining study drugs and empty packages will be collected at the end of the study.

The study will have three phases: the screening period, the initial treatment period, and the maintenance treatment period. The interventions in each phase are described below:Screening: No intervention.Initial treatment (weeks 1–8):Control group: rabeprazole and probiotic placebo. The samples will be distributed to the patients every month.Experimental group: rabeprazole and probiotics. The samples will be distributed to the patients every month.Rabeprazole dosage: 10 mg/tablet twice a day before meals;Dosage of probiotic placebo or LiHuo probiotics: 2 bars, once a day, with or without water (< 40 °C), after meals. Thus, the daily dosage of probiotics is more than 100 billion CUF. Participants who take antibiotics should wait 2 h before taking the probiotic placebo or LiHuo probiotics.Maintenance treatment (weeks 9–12):

Control group: probiotic placebo. The samples will be distributed to the patients every month.

Experimental group: probiotics. The samples will be distributed to the patients every month.

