### Primary outcome

Based on faeces, the GM from day 0 (week 0), day 28 (week 4), day 56 (week 8), and day 84 (week 12) will be evaluated. For the GM assessment, DNA will be extracted from the stool samples with the QIAamp Fast DNA Stool Mini Kit (Qiagen, Hilden, Germany) following the manufacturer’s instructions, and the DNA quality will be examined by agarose gel electrophoresis and a Nanodrop spectrophotometer. Shotgun metagenomic sequencing will be performed on all samples by using an Illumina HiSeq 2500 instrument. Libraries will be constructed from DNA fragments ~ 300 bp in length and paired-end reads will be generated by sequencing 150-bp lengths in the forward and reverse directions. Meanwhile, the metagenomic analysis will include several components: the analysis of alpha and beta diversities in each group to understand whether the differences in the microbiota compositions of groups are significant, as well as the taxonomic characteristics of the study and control groups at the phylum, genus, and species levels to identify specific genes related to the individual differences in GERD. Metagenomic biological pathway analysis will be used to evaluate the effect of probiotics on the function of gut metagenomics in patients with GERD and, hopefully, to explore the metagenomic biological pathways contributing to the mechanism of probiotics in the treatment of GERD.

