### Volunteer compliance monitoring

For the initial treatment (weeks 1–8), the sample package will include rabeprazole and probiotics or rabeprazole and the probiotic placebo; for the maintenance treatment (weeks 9–12), the sample package will include probiotics or the probiotic placebo. After the start of the study, the volunteers will receive a sample package at each monthly visit (package 1 at visit 1, package 2 at visit 2, and package 3 at visit 3) and will be required to return the package at the next visit such that the remaining rabeprazole, probiotics, or probiotic placebo doses can be counted to calculate the compliance level based on the equation below. Compliance ≥ 80% indicates good compliance.

Compliance = [actual amount taken (packets)]/[(amount prescribed (packets)] × 100%

To improve compliance, the study staff will use push messages via a WeChat group established for this study to remind the volunteers to take the sample as scheduled. All volunteers who complete the follow-up will receive 100 yuan as compensation. Moreover, rabeprazole will be provided at no cost during the study.

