### Statistical analysis

First, the intention-to-treat (ITT) analysis will be conducted between the two groups, including all the intended participants who do or do not complete the follow-up. Then, per-protocol (PP) analysis will be conducted in the four-subgroup datasets according to compliance (100%, ≥ 80%, 60–80%, and < 60%) to validate the robustness of the results. The datasets will be analysed as described below.

With a randomized block design, the nonparametric rank sum test and Friedman M test will be performed to analyse the difference in each outcome measure at each time point (see “Intervention Outcome Measures” for details) between the two groups, including the GM analysis, RDQ score, GSRS score, faecal metabolomics, and BMI. The significance level will be set to *P* = 0.05. Next, the paired Wilcoxon signed-rank test will be performed for pairwise intragroup comparisons to analyse the change trends for each outcome measure before, during, and after the probiotic intervention. The significance level will be set at *P* = 0.05/[k(k-1)/2], where k is the number of groups in the comparison. For analysis of the oesophagitis grade, the diagnosis of LA-B at baseline and LA-A at week 12 indicates that the patient's oesophagitis grade will have decreased by one level. If the grade is LA-C at baseline and LA-A at 12 weeks, the patient’s oesophagitis grade will have decreased by 2 levels. The number of oesophagitis grades reduced by 1 and 2 levels in each group will be calculated. Then, a chi-square (*χ*^2^) test will be performed. AE rates in the two groups will be compared by the *χ*^2^ test or Fisher’s exact probability test based on the occurrence frequency of AE, and the difference in treatment compliance will be also examined by the *χ*^2^ test.

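### Within-arm Wilcoxon tests are described as showing the course of the probiotic, but both arms start and stop rabeprazole, so these tests cannot isolate a probiotic effect

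*Protocol article*

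**What the plan says.** The Statistical analysis section begins with an intention-to-treat comparison of the two groups, using rank sum and Friedman tests on each outcome at each time point at 0.05. It then adds paired Wilcoxon signed-rank tests for "pairwise intragroup comparisons to analyse the change trends for each outcome measure before, during, and after the probiotic intervention". Their level is 0.05/[k(k-1)/2], "where k is the number of groups in the comparison". The abstract (Method) ends its list of assessment days with "day 84 (end of administration) to reveal intragroup differences". The Primary outcome section fixes four visits: "day 0 (week 0), day 28 (week 4), day 56 (week 8), and day 84 (week 12) will be evaluated".

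On treatment, Intervention strength and management gives, for weeks 1–8, "Control group: rabeprazole and probiotic placebo" and "Experimental group: rabeprazole and probiotics". Volunteer compliance monitoring adds that "for the maintenance treatment (weeks 9–12), the sample package will include probiotics or the probiotic placebo". The Exclusion criteria rule out, over the 2 weeks before entry, "Use of GERD-related drugs such as acid inhibitors, antacids, prokinetics, gastric mucosal protectors, and herbs", so day 0 is off acid suppression in both arms.

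Two further places matter. The abstract names the change in the gut microbiome as the primary measure. Note 11 to Table 1 starts the faecal metabolomics once the data show a significant probiotic effect on the microbiome, without naming the test that decides this.

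**The concern.** A signed-rank test in the experimental arm uses that arm's visits only. The probiotic and rabeprazole start together there, and the week 8 to week 12 interval coincides with rabeprazole leaving the package. No paired test in that arm can separate the two, yet the section labels the resulting trend as the course of the probiotic intervention. The article itself expects proton pump inhibitors to alter the microbiota (Background). Patients without oesophagitis enter on an RDQ score of at least 12, so regression to the mean is also likely for symptoms. In addition, day 84 is the end of administration, so no visit falls after the probiotic.

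This is more than loose wording. For the microbiome, symptom scores, metabolome and BMI, the within-arm test is the only analysis that the section ties to change, and change is how the primary measure is defined. As written, a within-arm result driven by rabeprazole could be reported as a probiotic effect, or could trigger the metabolomics.

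**Working it through.** **1. The plan's own figure.** Sample size gives a Chao1 difference of 145, SD 230, α = 0.025 and β = 0.20. Using n = 2[SD(z₁₋α/₂ + z₁₋β)/δ]²:

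2 × [230 × (2.241 + 0.842)/145]² = 2 × 4.890² = 47.8 per group, and 47.8 × 1.2 = 57.4.

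The article states 47.9 and 57.5, so the figure reproduces with α = 0.025 two-sided. It concerns a between-group difference; no error rate or power is stated for the within-arm tests. Carried forward: SD 230, and 60 × 0.8 = 48 completers per arm.

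**2. What changes between visits.**

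| Period | Experimental arm | Control arm |
|---|---|---|
| Day 0 | no acid inhibitor for 2 weeks, no powder | same |
| Weeks 1–8 | rabeprazole + probiotic | rabeprazole + placebo |
| Weeks 9–12 | probiotic | placebo |

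Let R be the rabeprazole effect, T time and regression to the mean, and P the probiotic effect. From week 0 to week 8 the expected change is R + T + P in the experimental arm and R + T in the control arm. The within-arm test asks whether R + T + P = 0. Only the difference between arms returns P.

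**3. Level.** If k is the four visits, 0.05/(4 × 3/2) = 0.05/6 = 0.0083. If k = 2, the level is 0.05. The article does not settle which; the point holds with either.

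**4. Rejection rate with P = 0.** Let d be the common shift in SDs of the paired change. For normal changes the signed-rank rejection rate is approximately Φ(d√(3n/π) − z₁₋α/₂). With n = 48, √(3 × 48/π) = 6.770, and z = 2.638 at 0.0083.

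- d = 0.3: Φ(2.031 − 2.638) = 27%; simulation 26%
- d = 0.5: Φ(3.385 − 2.638) = 77%; simulation 74%
- d = 0.8: simulation 99%
- 50% is reached at d = 2.638/6.770 = 0.39

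At level 0.05 the simulated rates are 51%, 91% and 100%.

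**5. In Chao1 units.** The SD of the paired change is 230√(2(1 − ρ)): 272, 230 and 178 for visit correlation ρ = 0.3, 0.5 and 0.7. The 50% point (d = 0.39) is then a common shift of about 106, 90 and 69 units. Simulation used 2,000 trials per setting, 48 per arm, no probiotic effect, the same shift D in both arms at weeks 4 and 8, and ρ from 0.3 to 0.7. Both D and ρ are assumed.

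| D (in visit SDs) | Week 0 vs 8 at 0.0083 | Week 0 vs 8 at 0.05 |
|---|---|---|
| 0 | 0.4–1% | 4–6% |
| 36 (0.16) | 4–10% | 14–27% |
| 72.5 (0.32) | 17–51% | 41–78% |
| 115 (0.50) | 52–94% | 79–99% |
| 145 (0.63) | 78–99.9% | 94–100% |

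Week 0 versus week 12 at 0.0083 stays at 0.4–1% if the shift has fully reversed by week 12. The between-arm rank sum test at 0.05 rejects in about 4–6% of trials at weeks 8 and 12 throughout.

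**6. Significant in exactly one arm.** With the same rejection rate p in both arms this is 2p(1 − p). At 0.0083: 2 × 0.26 × 0.74 = 38% at d = 0.3, the same at d = 0.5 (p = 0.74), and 2 × 0.99 × 0.01 = 2% at d = 0.8. At 0.05: 2 × 0.51 × 0.49 = 50% at d = 0.3, and 2 × 0.91 × 0.09 = 16% at d = 0.5. The pattern is common at moderate shifts and rare at large ones.

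**The case against.** The strongest reply is that the between-arm comparison already leads. The trial is a superiority study sized on week 12 differences between groups, and the between-group tests come first in the Statistical analysis section. The paired tests follow, to analyse trends, and the reference to the probiotic intervention can be read as a time label. All of this stands. A reader might infer that the plan takes a within-arm P value as proof of efficacy; no section says so. Nor is the main comparison compromised: under randomisation, comparing arms at week 12 is valid without change scores.

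A reader might also infer that the within-arm tests will be significant in most trials even if the probiotic is inert. The documents do not support that without a condition. They give no rabeprazole shift for Chao1, Shannon, RDQ or GSRS and no visit correlation, and at small shifts, or at week 12 after full reversal, the claim is false. Where the shift is large, both arms will usually be significant, and the control arm then exposes the common cause.

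The reply does not remove the mislabelling. The stated purpose in the abstract is within-group, the trend is attributed to the probiotic, and the metabolomics trigger does not name the between-arm test. These are statements in the text, not details lost in condensing a protocol.

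**Conclusion.** The point holds in a limited form. The within-arm tests cannot separate the probiotic from the start and stop of rabeprazole, time or regression to the mean, and describing them as the course of the probiotic intervention is wrong. Taken as tests of a probiotic effect, their false-positive rate is uncontrolled. For week 0 versus week 8 at 0.05/6 with 48 per arm it runs from about 1% with no common shift to above 90% with a large one, crossing one half at about 0.4 SD of the paired change. These rates rest on normal changes, k = 4 and an assumed shift. The between-arm test, the sample size and the main error rate are unaffected. Severity is moderate: it changes what may be concluded from the supporting analyses and what may trigger the metabolomics, not the validity of the main comparison.

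**What to change.** In the abstract, replace the intragroup purpose of the repeated assessments with between-group differences in change from day 0.

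In Statistical analysis:
- Add a between-arm comparison at each visit that uses the day 0 value, preferably baseline-adjusted (for example a rank-based ANCOVA).
- State that evidence of a probiotic effect, including the trigger for metabolomics in note 11 to Table 1, comes only from the between-arm comparison.
- Keep the paired Wilcoxon tests as a description of the course on rabeprazole plus probiotic or placebo, labelled by visit week.
- State that significance within one arm, or in one arm only, will not be read as a probiotic effect.

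The cost is a few sentences and one analysis of data already being collected, ideally settled before unblinding. The downside is that within-arm P values can no longer support a claim. Baseline adjustment is a preference: it matches the definition of the primary measure as a change, but the unadjusted between-arm test is also valid.

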### Study intervention

The study treatment consists of two phases: an initial treatment period lasting 8 weeks (weeks 1–8) and a maintenance treatment period lasting 4 weeks (weeks 9–12). The patients will be randomized into two groups: a control group and an experimental group. The participants will not know the group to which they have been assigned.

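### The within-arm correction defines k as the number of groups, which read as the two arms leaves 0.05 uncorrected, and the stated 0.05 covers the metagenomic and metabolomic tests without adjustment

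*Protocol article*

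**What the plan says.** All references are to the protocol article.

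- **Between-group tests (Statistical analysis).** Rank-based tests are planned "to analyse the difference in each outcome measure at each time point", "including the GM analysis, RDQ score, GSRS score, faecal metabolomics, and BMI". The level is one line: "The significance level will be set to *P* = 0.05". No adjustment over features, outcomes or visits is attached to it.
- **Within-group tests (Statistical analysis).** Next, "the paired Wilcoxon signed-rank test will be performed for pairwise intragroup comparisons", to describe trends before, during and after the intervention. The level is 0.05/[k(k-1)/2], "where k is the number of groups in the comparison".
- **What a group is (Study intervention).** "The patients will be randomized into two groups: a control group and an experimental group". The Statistical analysis section uses the word in the same sense when it speaks of the two groups.
- **Occasions (Primary outcome, Secondary outcome).** The gut microbiome, faecal metabolome, RDQ and GSRS are each assessed at weeks 0, 4, 8 and 12.
- **What the microbiome and metabolome analyses contain.** The Primary outcome section lists alpha and beta diversity, "taxonomic characteristics of the study and control groups at the phylum, genus, and species levels", and pathway analysis. The Secondary outcome section adds a search for differential metabolites and their correlation with the microbiota. Neither section says how many features there are.

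**The concern.** Two written rules do not fit the tests they govern.

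First, a paired test within one arm compares visits, so the number of comparisons depends on the number of visits. The rule ties it to the number of groups, a word the article otherwise uses for the trial arms. An analyst who follows the text can reach a divisor of 1 and apply no correction. The abstract gives intragroup differences as the purpose of the repeated assessments, so these results are likely to be reported.

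Second, a single unadjusted 0.05 is stated for a list of outcomes of very different kinds. For a questionnaire total or BMI it governs one test per visit. For the microbiome and metabolome it extends, as written, to analyses made up of many taxa, pathways and metabolites. Lists of nominally significant features would then contain chance findings, and those lists feed the mechanistic conclusions that both outcome sections aim for.

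**Working it through.** The article gives the within-group threshold only as a formula, so there is no evaluated figure to reproduce.

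**1. Within-arm threshold**

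Inputs: two groups (Study intervention); four occasions (Primary and Secondary outcome). Number of pairs m = k(k-1)/2; threshold = 0.05/m.

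| Reading of k | k | m | Threshold |
|---|---|---|---|
| One arm, taken strictly | 1 | 0 | undefined |
| Two trial arms | 2 | 1 | 0.05 |
| Before, during, after as three occasions | 3 | 3 | 0.0167 |
| Four visits | 4 | 6 | 0.0083 |

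One sentence therefore supports thresholds from 0.05 down to 0.0083.

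**2. What the divisor changes**

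Take four visits with no change over time, equal variances and equal correlations between visits, and test all six pairs.

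- If the six tests were independent: 1 - 0.95^6 = 0.265 at 0.05, and 1 - (1 - 0.0083)^6 = 0.049 at 0.0083.
- The pairs share visits, so they are not independent. The normal-theory distribution of the range of four means gives 20.3% at 0.05 and 4.1% at 0.0083.
- Simulated signed-rank tests under the same null, with 48 or 60 patients, gave between 20% and 23% at 0.05, and about 4% at 0.0083.

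So the chance of at least one false positive is about 20% per outcome per arm uncorrected, and about 4% corrected.

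**3. Between-group tests on features**

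With m features that do not differ, the expected number with P < 0.05 at one visit is 0.05 x m. The article gives no m, so the counts below are assumptions.

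| Assumed null features m | Expected false positives per visit |
|---|---|
| 100 | 0.05 x 100 = 5 |
| 300 | 0.05 x 300 = 15 |
| 1000 | 0.05 x 1000 = 50 |

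The expected count does not depend on correlation between features. At m = 100, the chance of at least one false positive would be 1 - 0.95^100 = 0.994 if the features were independent.

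**The case against.** **The intent is visible.** The formula is an all-pairs Bonferroni correction placed directly after the mention of pairwise intragroup comparisons. It would serve no purpose with k = 2, so the groups in the comparison most sensibly mean the sets of measurements compared. This stands as to intent. A reader might infer that the plan has no multiplicity control at all, but a correction is written down, so the text does not support that. What remains is that the wording also permits 0.05, and that even the occasions reading leaves three or four open.

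**The no-change null is hard to believe here.** Both arms take rabeprazole in weeks 1-8 and stop it for weeks 9-12, and the trial's rationale is that such drugs alter the microbiome. Reflux symptoms should move as well. This stands. The 20% figure measures what the divisor does; it does not forecast the error rate for the microbiome or RDQ. Combining the arms to get 1 - (1 - 0.203)^2 = 0.365 would need that null in both arms at once, so it should not be presented as the trial's error rate. The within-arm tests are also secondary to the randomised comparison.

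**Feature-level methods belong in an analysis plan that is not shown.** The 0.05 is written per outcome measure, and the article does not say that each species or metabolite is judged at raw 0.05. This stands in part: a missing choice of false-discovery method would be no finding by itself. But the article states a level and names the microbiome and metabolomics analyses as within its scope, so a later adjustment would change a published rule. A reader might also infer that hundreds of features will be tested; the documents give no count.

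**Other safeguards exist.** Table 1, footnote 11, makes metabolomics conditional on a significant microbiome effect, and the Sample size section plans on Chao1 and Shannon at week 12 with alpha 0.025. The condition does not control error among metabolites once they are tested, and it does not say which microbiome test triggers it. The purpose of 0.025 is not stated, and the analysis section uses 0.05.

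**Conclusion.** The point holds in two limited parts.

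1. The definition of k does not fit the within-arm tests. Read as trial arms it leaves 0.05 in place; read as four visits it gives 0.0083. The difference is about 20% against about 4% familywise error per outcome per arm, assuming no change over time and all six pairs tested. It concerns secondary, descriptive comparisons and is probably a slip of wording.
2. The stated 0.05 extends to the microbiome and metabolome analyses at each visit without adjustment. The size depends on an unknown feature count: about 0.05 x m false positives per visit, which is 5 for an assumed 100 null features and 50 for 1000.

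Neither part calls into question the stated level for a single diversity index or clinical score. Both should be corrected before analysis, because the threshold and the list of significant features should not be open to choice once the data are seen.

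**What to change.** - **Within-arm tests.** Define k as the number of time points compared: k = 4, six pairs, threshold 0.05/6 = 0.0083. Alternatively, compare only weeks 4, 8 and 12 with baseline and use 0.05/3 = 0.0167. State which, and say that these tests are descriptive and do not carry the treatment comparison.
- **Feature-level tests.** Keep the stated level for the diversity indices and clinical scores. For taxa, pathways and metabolites, apply Benjamini-Hochberg at a 5% false discovery rate within each feature family (each taxonomic level, pathways, metabolites) and report q-values.

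The cost is about three sentences in the Statistical analysis section, with no new data and no change to the sample size. The downside is that fewer visit differences and fewer features will be called significant.
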